#### Maintenance intervention by SMS

At the 3 month point, participants are randomly assigned to SMS support or CBT without SMS support. Participants will be sending weekly self-monitored information regarding their diet, physical activity and emotions by SMS to the mental health professional for the next 9 months (Table 4).

**Table 4 Tab4:** Text message plan

1) How many hours of exercise did you had in the past week? For example cycling or walking	
A) Less than 1 h	
B) 1 to 3 h	
C) 4 to 6 h	
D) 7 to 10 h	
E) More than 10 h	
2) How many days did you keep up a healthy diet in the past week?	
A) None of the 7 days	
B) 1 to 2 days	
C) 3 to 4 days	
D) 5 to 6 days	
E) All 7 days	
3) How often did you felt satisfied about yourself in the past week?	
A) Never	
B) Almost never	
C) Sometimes	
D) Often	
E) Always	
4) How often did you felt sad or unhappy in the past week?	
A) Always	
B) Often	
C) Sometimes	
D) Almost never	
E) Never	
5) What is your weight today in kilograms? For example 88,4 kg	

A semi-automated software program generates feedback in response to the incoming messages. These feedback messages provide social support, encourage positive behaviour and empower behavioural strategies. The mental health professional assesses whether the suggested feedback is applicable before sending it to the participant. In addition, participants receive two messages per week addressing eating behaviour (self-monitoring, barriers, binge eating, eating pace, emotional eating, food choices, portions, planning, preparation, stimulus control, social eating, sugar sweetened beverages) and physical activity (motivation, fun facts, sedentary behaviour). There are five types of messages, as shown in Table 5.

**Table 5 Tab5:** Types of text messages

• Tips (i.e. Going grocery shopping today? Don’t go if you’re hungry!)
• Reminders (i.e. Read the flyer about the Dutch food guide again. What’s your focus this week?)
• Educational facts (i.e. Did you know that cleaning the house is also a moment of exercise? You can burn up to 140 calories in an hour!)
• Motivational messages (i.e. Are you not completely satisfied with your diet today? Tomorrow is new day, don’t give up!)
• Knowledge based (i.e. Do you know the second step in writing a thought record?)

### Control group: usual care

Just like the lifestyle intervention group, the control group visits the hospital after the initial assessment during the 4 consecutive occasions at which they are similarly assessed as the CBT lifestyle intervention group. During these 5 measurement moments they have a short, unstructured consult with their treating physician. Participants in the control group are encouraged to lose weight through publicly available services (i.e. diets, visiting a dietician, going to the gym or participating in public programs such as Weight Watchers®) and use simple strategies, including self-monitoring of their diet. The physician also mentions the risk of overweight for both mother and child, and the relation between overweight and fertility. If patients fail to achieve their target weight during the 12-month study period (see below), they can participate in the lifestyle intervention, but are not included in the trial.

At the Erasmus MC, patients diagnosed with PCOS receive ovulation induction treatment when shifted to a lower BMI category. Meaning: 1) a weight loss of 4.0 BMI points; 2) a BMI < 34.0; and 3) weight loss maintenance over 3 months. The intervention group receives ovulation induction treatment after 1) a weight loss of 4.0 BMI points; 2) a BMI < 34.0; and 3) complying with the intervention group for more than 1 year.

### Outcome measures

The primary outcome of this study is to test whether CBT provided by a mental health professional, working in a multidisciplinary team with a dietician and a physical therapist (a three-component intervention), is effective to decrease weight compared to usual care (control) at the end of the treatment. Secondary outcomes include: reproductive, drop-out, quality of life, healthy diet, physical activity, metabolic and endocrine improvements, the health of the (unborn) child. All outcome variables are measured at the start of the study, and again at 3 months, 6 months, 9 months and 12 months. All outcome measures are displayed in Table 6. Below we give more details about the collection of the secondary outcomes.

**Table 6 Tab6:** Outcomes measures (T0, T1, T2, T3, T4)

Primary outcome	
Weight in kilograms	
Secondary outcomes	
(1) reproductive outcomes:	a) cycle duration and frequency
	b) spontaneous pregnancies
2) anthropomorphometric outcomes:	a) BMI
	b) waist circumference (WC)
	c) hip circumference (HC)
	d)WC/HC ratio
(3) clinical and biochemical PCOS features:	a) hair growth pattern
	- Ferriman Gallwey score
	b) blood pressure
	c) transvaginal ultrasound outcomes
	- ovarian volume
	- follicle count
	- total follicles per ovary
	d) endocrine outcomes
	- insulin resistance
	- hyperandrogenism
	- dyslipidemia
(4) psychological outcomes:	a) eating behaviour and disturbances
	- The Dutch Eating Behaviour Questionnaire (NVE)
	- Eating Disorder Examination Questionnaire (EDE-Q)
	b) quality of Life
	- Short Form 36 (SF-36)
	- Polycystic Ovary Syndrome Questionnaire (PCOSQ)
	c) depression
	- Beck Depression Inventory (BDI)
	d) self-esteem
	- Rosenberg Self Esteem Scale (RSE)
	e) fear of negative appearance
	- Fear of Negative Appearance Evaluation Scale (FNAES)
	f) satisfaction
	- Self-constructed questionnaire
(5) physical activity:	a) perceived level of daily physical activity
	- the International Physical Activity Questionnaire (IPAQ)
	b) the intervention group: submaximal bicycle test
(5) physical activity:	a) food intake
	-energy (calories)
	- protein
	- fat
	- saturated fat
	- carbohydrates
	- mono- and disaccharides
	- drinks (ml)
(7) other:	- attendance at meetings
	**-** drop-out and reasons for drop-out

#### Psychological outcomes

##### Eating behaviour and disorders

The Dutch Eating Behaviour Questionnaire (DEBQ) is a validated questionnaire; it is administered to assess restrained eating (10 items), emotional eating (13 items), and external eating (10 items). Subscales are computed as the mean of the relevant questions resulting in a score between 1 and 5, with a higher score reflecting a higher degree of the relevant eating behaviour [58]. Additionally, the Eating Disorder Examination Questionnaire (EDE-Q) is used to measure specific eating disorders. This questionnaire consists of 36 items measuring five subscales: concerns about shape, weight, and eating, in addition to restrained and binge eating. The subscale scores range between 0 and 6. A higher score indicates more severe eating psychopathology [59].

##### Quality of life

The Short Form 36 (SF-36) is a generic quality of life questionnaire that consists of 36 questions. Quality of life is divided into in eight dimensions: physical functioning, role-physical, bodily pain, general health, vitality, social functioning, role-emotional and mental health. The sum of the SF-36 item scores within each dimension is transformed into a scale ranging from 0 (poor health) to 100 (good health) [60].

The Polycystic Ovary Syndrome Questionnaire (PCOSQ) is a specific health-related quality of life (HRQoL) questionnaire for PCOS women [13]. This questionnaire consists of 26 questions and five domains: emotions, body hair, weight, infertility and menstrual problems. Each item is scored on a scale between 1 and 7, whereby 1 indicates the worst health status and 7 denotes best health status. We have translated this questionnaire into Dutch. This questionnaire has not yet been validated.

##### Depression

The Beck Depression Inventory (BDI) [61] is a validated questionnaire that measures depression and depressive symptoms according to the criteria of the DSM-IV [62]. The Dutch BDI-II [63] questionnaire consists of 21 questions for the evaluation of cognitive, affective and somatic symptoms of depression. Higher total scores indicate more severe depressive symptoms.

##### Self-esteem and body image

Self-esteem is measured by the Rosenberg Self Esteem Scale. This questionnaire consists of 10 questions and has been validated for the Dutch population [64]. The RSES measures global self-esteem. Items are scored on a 4-point scale. Scores below 21 indicate low self-esteem. The Fear of Negative Appearance Evaluation Scale (FNAES) [65] is a short questionnaire consisting of six items that measure body image, eating disorder and depression. The items are answered on a five-point Likert scale, ranging from ‘not at all’ to ‘extremely’, whereby a higher score indicates more fear of negative evaluation by others. The Dutch version has not been validated yet.

#### Dietary outcomes

Food intake is documented at home on paper, in a 3 day (including 1 weekend day) food diary to determine changes over time in food intake, meal and eating pattern, meal frequency, amount of carbohydrates, vegetables, fruit, dairy and snacks. Additionally, using a self-constructed questionnaire according to the dietary history method [66], participants are asked about:Weight: i.e. birth weight, highest weight, development of obesityDieting: i.e. history of weight loss dieting and how much weight loss was achievedHistory of eating: i.e. how parents dealt with food while growing upEating pattern: i.e. watching TV while eating, amount of take-out foods

The validity of the dietary history method during weekdays has been proven, and it is less reliable during weekends [67].

The Dutch Food Composition Database (NEVO) is used to calculate the nutritional composition of each 3 day food record. This database contains information on food products and meals that are regularly eaten by a large proportion of the Dutch population.

#### Physical activity outcomes

To gain insight into the perceived level of daily physical activity, we use the International Physical Activity Questionnaire (IPAQ) [68]. This questionnaire consists of 31 items about the frequency and duration of physical activity at work, during transportation, during household activities and during leisure time in the course of the previous week.

A continuous progressive submaximal test is used to determine the exercise intensity and the fitness progress in the intervention group. The maximum heart rate and the maximum load are determined during this test. Firstly, the resting heart rate is measured when sitting in a chair. Secondly, the heartrate is measured using a standard ramp protocol on a bicycle after a 5 minute warm-up (20 watt) on a bicycle. Thirdly, the load is increased every minute with 10, 15 or 20 watt, based on the level of the participant. During the test, the participant must maintain a speed of 60 to 80 revolutions per minute. The test is stopped when the speed is decreased by 15 revolutions per minute. The response to the submaximal test is evaluated immediately after the test by the modified Borg scale [69]. This scale ranges from 0 to 10 and provides insight into the perceived exertion level.

Prior to the submaximal test, the treating physician will examine contraindications (cardiac and/or pulmonary problems) using the Physical Activity Readiness Questionnaire (PAR-Q) [70]. In case of the slightest suspicion of cardiac and/or pulmonary problems the submaximal test is not performed.

### Sample size calculation

The original sample size calculation in 2009 was based on an anticipated effect of a difference between the groups of 0.45 in terms of Cohen’s d in the primary outcome variable (BMI), with a power (1-beta) of 0.80 and an alpha level of 0.05 (two-sided) in a 2:1 ratio. This ratio was required for analysis of the secondary outcome: the effect of SMS within the intervention group. This resulted in 156 patients to be enrolled in the intervention group and 78 patients in the control group, a total of 234. This number was registered at the Dutch Trial Registry (TC 2450). On behalf of the Grant Foundation (MRace), an interim analysis was performed in May 2014. After inclusion of 150 patients, we applied an interim power analysis to the complete cases. The control group had a reduction from 33.3 ± 6.8 kg/m^2^ to 32.6 ± 6.6 kg/m^2^, an effect of Cohen’s d = 0.10, whereas the lifestyle intervention group showed a reduction from 33.8 ± 4.8 kg/m^2^ to 31.3 ± 5.1 kg/m^2^, an effect of d = 0.52 and a difference of 0.42. For the sample size calculation, we applied the method described by Aberson [71], with a power of 0.90, a two-sided alpha of 0.025 (corrected for the interim analysis) and five repeated measures linearly decreasing. We observed an intercorrelation of about 0.90 between all measurements. Maintaining a ratio of 2:1, the required sample is 84 participants in the lifestyle intervention and 42 in the control group, a total of 126 complete cases. With an observed drop-out proportion of 40%, a total of 210 participants are needed for the study. We anticipated to have a relatively high drop-out rate, because pregnancy leads to exclusion. Note that this sample size calculation is a conservative number, as it is based on a complete case analysis of variance. The intended multilevel analysis provides more power.

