**Methods:**

The present study is a longitudinal randomized controlled trial (RCT) to study the effectiveness of a three-component 1-year cognitive-behavioural lifestyle intervention in overweight/obese women with PCOS. A total of 210 participants are randomly assigned to three groups: 1) CBT provided by the multidisciplinary team or; 2) CBT provided by the multidisciplinary team and Short Message Service (SMS) or; 3) usual care: encourage weight loss through publicly available services (control group). The primary aim of the 12-month intervention is to explore whether a three-component 1-year cognitive-behavioural lifestyle intervention is effective to decrease weight, when compared to usual care. Secondary outcomes include: the effect of the intervention on the PCOS phenotype, waist circumference, waist to hip ratio, ovulation rates, total testosterone, SHBG, free androgen index (FAI), AMH, hirsutism, acne, fasting glucose, blood pressure and all psychological parameters. Additionally, we assessed time to pregnancy, ongoing pregnancies, clinical pregnancies, miscarriages and birth weight.

All outcome variables are measured at the start of the study, and again at 3 months, 6 months, nine months and 12 months.

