### Randomisation

At the baseline, after the initial assessment, participants are randomized at a 2:1 ratio into the following groups: 1-year CBT lifestyle intervention with SMS (*n* = 78), 1-year CBT lifestyle intervention without SMS (*n* = 78), or the control group who receives usual care (*n* = 78) using a computer-generated random numbers table. A research nurse, who is not involved in the study, carries out the randomisation. Assignment is made by sequentially numbered, identical, sealed envelopes, each containing a letter designating the allocation (i.e. “A” for intervention with SMS, “B” for intervention without SMS and “C” for control,).

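### The 2009 sample size of 156 + 78 does not follow from its stated inputs (177 at power 0.80; about 0.90 power at 234), and the Randomisation section still allocates 234 where the plan is now 210

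*Protocol article*

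**What the plan says.** The Sample size calculation section of the protocol article describes two calculations.

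- **2009, labelled as original.** It was "based on an anticipated effect of a difference between the groups of 0.45 in terms of" Cohen's d, "with a power (1-beta) of 0.80 and an alpha level of 0.05 (two-sided) in a 2:1 ratio". The ratio is explained by the SMS question: "This ratio was required for analysis of the secondary outcome: the effect of SMS within the intervention group". The outcome is stated as a direct consequence of these inputs: "This resulted in 156 patients to be enrolled in the intervention group and 78 patients in the control group, a total of 234". No drop-out allowance is given for this calculation. The section adds that this number was entered in the Dutch trial registry.
- **2014, after an interim analysis.** "the required sample is 84 participants in the lifestyle intervention and 42 in the control group, a total of 126 complete cases". Then: "With an observed drop-out proportion of 40%, a total of 210 participants are needed for the study".

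The abstract (Methods) uses the revised total: "A total of 210 participants are randomly assigned to three groups". The Randomisation section, written in the present tense, gives a 2:1 ratio and 78 women in each of three groups, including "the control group who receives usual care (*n* = 78"). That makes 234.

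**The concern.** Every input of the 2009 calculation is printed, so a reader can repeat it, and the printed answer does not come out. The gap of 57 patients is too large for rounding or choice of formula. At least one of the power, the ratio or an undeclared drop-out allowance is therefore misdescribed. The article says 234 was registered, so it is the number against which achieved enrolment will naturally be compared, and its justification should reproduce.

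The second matter needs only addition. The operative description of allocation carries one total and the current sample size plan carries another, and nothing in the Randomisation section marks its numbers as out of date.

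**Working it through.** **Inputs** (Sample size calculation, 2009): d = 0.45; two-sided alpha 0.05 (z = 1.960); power 0.80 (z = 0.842); intervention to control 2:1; no drop-out allowance stated.

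**Step 1: the 2009 figure from its own inputs.** With k intervention patients per control patient, the control group size is

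n_control = (1 + 1/k) × (z_alpha + z_power)² / d².

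For k = 2 and power 0.80: 1.5 × (1.960 + 0.842)² / 0.2025 = 58.1, so 59 control and 118 intervention, total **177**. The noncentral t-test gives 58.8 control, so again 59. The stated 234 is not reproduced. The gap is 234 − 177 = 57, and 57/177 = 32%.

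**Step 2: power of the stated size.** For 156 against 78 the standard error in SD units is √(1/156 + 1/78) = 0.1387. Then 0.45/0.1387 − 1.960 = 1.285, which is power **0.901** (noncentral t 0.898). This assumes that all 234 are analysed.

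**Step 3: which change of input gives 78 or 234?**

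| Variant (d = 0.45) | Control or per arm | Total |
|---|---|---|
| 2:1, two-sided 0.05, power 0.80 (as stated) | 59 | 177 |
| 2:1, two-sided 0.05, power 0.90 | 77.8, so 78 | 234 |
| 1:1 between two single arms, two-sided 0.05, power 0.80 | 77.5, so 78 | 234 with a third arm of 78 |
| 2:1, power 0.80, then 25% drop-out: 177/0.75 | – | 236 |
| 2:1, one-sided 0.05, power 0.80 | 46 | 138 |
| 2:1, two-sided 0.025, power 0.80 | 71 | 213 |

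Two variants give 78 exactly under the normal formula; the t-test gives 78.5 for each. In the 1:1 case, 78 against 78 has power 0.802 (noncentral t 0.797). The drop-out variant only comes close: the exact implied allowance is 1 − 177/234 = 24.4%, a figure back-solved here and found nowhere in the document.

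**Step 4: how drop-out affects the 0.90.** If the analysed numbers fall in proportion, the power of 156 against 78 becomes about 0.80 with 25% loss and about 0.71 with the 40% observed later.

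**Step 5: the current total.** The revised figure reproduces: 126/(1 − 0.40) = 210. By group, 84/0.60 = 140 intervention and 42/0.60 = 70 control. The Randomisation section gives 3 × 78 = 234. The difference is 234 − 210 = 24, or 8 per arm if the three arms are equal.

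**The case against.** The strongest reply is that power 0.80 may be correct. A 1:1 comparison of single arms at power 0.80 needs 78 per arm, which is the per-arm number in the Randomisation section, and the SMS comparison inside the intervention group is such a comparison. On that account the power is right and the described ratio is wrong. This stands as a possibility, so the statement that the power was misreported cannot be made outright. It does not rescue the sentence as printed, which describes a 2:1 calculation, while the primary hypothesis pools the intervention with and without SMS against usual care.

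The second reply is that the 2009 calculation is history. That is correct: the section labels it as original and replaces it with a calculation that reproduces. No current target or alpha level depends on it. For the pooled comparison the discrepancy is also conservative if all 234 are analysed.

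Third, the document itself explains both totals and says that 210 are needed. A reader might infer that 24 women too many will be randomised. The text does not support that: the abstract and the revised calculation agree on 210, and 78 per arm reads as an original allocation left unrevised. The Randomisation section is nevertheless current text, and it disagrees with both.

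**Conclusion.** The point holds as a matter of reporting accuracy.

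- The stated 2009 inputs give 177, not 234, and 156 against 78 has about 0.90 power for the pooled comparison before drop-out. This rests on a two-group comparison of means with d = 0.45, two-sided alpha 0.05 and no loss.
- The documents do not show whether the power, the ratio or an unreported drop-out allowance is the misstated element.
- The allocation numbers in the Randomisation section exceed the current planned total by 24.

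Two stronger conclusions are tempting and unsupported. One is that a wrong power was registered: the article says only that the number 234 was registered and mentions no registered power. The other is that the present design is invalid or wrongly sized because of this error: the current 210 comes from a separate calculation and does not use the 2009 power.

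**What to change.** 1. In the Sample size calculation section, state which calculation was done in 2009 and correct the matching element:
   - power 0.90 at 2:1 before drop-out; or
   - power 0.80 for a 1:1 comparison of single arms of 78, adding that the pooled 156 against 78 then has about 0.90 before drop-out; or
   - power 0.80 at 2:1 with the drop-out allowance that was actually used.

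   The sponsor must choose from its own records. The document does not settle it.
2. In the Randomisation section, align the numbers with 210: 140 intervention and 70 control at 2:1, which is 70 per arm if the two CBT arms are equal. Alternatively, mark 78 per arm as the original, superseded target. The section on SMS maintenance places the SMS assignment at 3 months rather than at baseline, so the text should also make clear to which point the split of the 140 refers.

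Both are text corrections. They change no data collection, analysis or enrolment under the current plan of 210.

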### Statistical analyses

Mixed modelling will be applied for longitudinal analyses of the data by using SPSS version 21. Mixed modelling can efficiently deal with missing data and unbalanced time-points [72]. This analysis will include two levels: the patients will constitute the upper level, and their repeated measures the lower level. First, for each outcome variable a saturated model will be postulated, with the primary or/and secondary outcomes as dependent variables. The saturated models will include treatment group, time, quadratic time, logarithm of time, and all treatment-time interactions as fixed effects. The deviance statistic [73] using restricted maximum likelihood [74] will be applied to determine the covariance structure. Next, the saturated fixed part of the models will be reduced by eliminating insignificant fixed effects using Wald tests, respecting that interaction effects must be nested under their main effects [75]. The significance of the difference between the saturated models and the parsimonious final models will be determined with the deviance statistic using ordinary maximum likelihood. The residuals of the model will be checked for normal distribution, which is necessary for a correctly fitted mixed model. Effect sizes will be calculated by dividing the differences between time-point and baseline estimations and the estimated baseline standard deviation. The definition of Cohen will be used for the interpretation of the effects sizes: an effect size of 0.20 is considered a small effect, 0.50 medium and 0.80 a large effect [76].

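### The interim effect of 0.42 subtracts two within-arm changes standardised by different SDs; on a common SD it is about 0.32, and 126 completers cannot be reproduced from 0.42 as stated

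*Protocol article*

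**What the plan says.** The Sample size calculation section first describes the 2009 calculation, which assumed a between-group Cohen's d of 0.45 in BMI. It then describes a recalculation after 150 inclusions, based on complete cases. For control it gives: "The control group had a reduction from 33.3 ± 6.8 kg/m^2^ to 32.6 ± 6.6 kg/m^2^, an effect of Cohen’s d = 0.10". For the lifestyle arm it gives a "reduction from 33.8 ± 4.8 kg/m^2^ to 31.3 ± 5.1 kg/m^2", followed by "an effect of d = 0.52 and a difference of 0.42".

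The new sample size uses a cited method "with a power of 0.90, a two-sided alpha of 0.025 (corrected for the interim analysis"), "five repeated measures linearly decreasing", and a correlation of about 0.90 between all measurements. The result is that "the required sample is 84 participants in the lifestyle intervention and 42 in the control group, a total of 126 complete cases". Dividing by the 60% expected to complete gives 210. The section adds that "this sample size calculation is a conservative number", because it rests on a complete-case analysis of variance while the planned multilevel analysis has more power.

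The Statistical analyses section obtains effect sizes by "dividing the differences between time-point and baseline estimations and the estimated baseline standard deviation" and interprets them on Cohen's scale.

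**The concern.** A standardised between-group effect needs one denominator. Here each arm's change is divided by that arm's own baseline SD, and the SDs differ widely (6.8 against 4.8). The subtraction credits the intervention with a larger effect partly because its women were more alike at baseline. A reader who sees 0.45 and then 0.42 in the same paragraph will conclude that the interim data nearly confirmed the planning assumption. That comparison is not like with like.

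The second question is whether 0.42 and 126 belong together. If the stated effect does not lead to the stated sample size, nobody can tell what difference the trial is sized to detect.

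**Working it through.** **Inputs (all from the Sample size calculation section).** Control BMI 33.3 (SD 6.8) to 32.6 (6.6). Intervention BMI 33.8 (4.8) to 31.3 (5.1). Power 0.90, two-sided alpha 0.025, five measures with a linear decline, r about 0.90, allocation 2:1.

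**1. Reproduce the stated effects.**
- Control: (33.3 − 32.6)/6.8 = 0.7/6.8 = 0.103.
- Intervention: (33.8 − 31.3)/4.8 = 2.5/4.8 = 0.521.
- Difference: 0.521 − 0.103 = 0.418, the stated 0.42.

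The baseline SD of each arm is thus the denominator of its own effect.

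**2. Put the contrast on one SD.**
- Difference in change: 2.5 − 0.7 = 1.8 kg/m².
- Baseline SD pooled 2:1: √[(2 × 4.8² + 6.8²)/3] = 5.55.
- d = 1.8/5.547 = 0.324.
- With the control SD alone: 1.8/6.8 = 0.26. With the intervention SD alone: 1.8/4.8 = 0.375.

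Neither arm's baseline SD, nor their pooled value, gives 0.42. Against the pooled value, 0.42 is 29% too high (0.42/0.3245 = 1.29).

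**3. Try to reproduce 126.** For a group-by-time F test with 4 numerator df, a linear separation from 0 at baseline to d at the last visit, equal correlation r and 2:1 allocation, the noncentrality is

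λ = N × (2/9) × 0.625 × d²/(1 − r).

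The 0.625 is the sum of squared deviations of 0, ¼, ½, ¾, 1. At d = 0.42, r = 0.90 and N = 75, λ = 75 × 0.2222 × 0.625 × 0.1764/0.10 = 18.4, which gives power of 0.90.

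Total completers for power 0.90 at two-sided alpha 0.025, r = 0.90:

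| Test | d = 0.42 | d = 0.3245 |
|---|---|---|
| Group-by-time, univariate, sphericity | 75 | 123 |
| Group-by-time, multivariate | 81 | 129 |
| Change score | 66 | 108 |
| ANCOVA | 63 | 102 |
| Linear slope | 51 | 87 |
| Single time point | 318 | 531 |

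Nothing in the 0.42 column is near 126.

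**4. What would reach 126 from 0.42.** Two changes to the univariate group-by-time test do so: a sphericity epsilon of 0.5 gives 123, and r = 0.83 with sphericity gives 126. The article states neither. Equal correlations of 0.90 with similar variances imply epsilon near 1, so the first sits badly with the text. The second departs from the stated value of about 0.90.

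**5. Power of 84 + 42 completers.** The group-by-time test has 99.4% power at 0.42. At 0.3245 it has 90.9% (univariate) or 89.7% (multivariate). A change-score test of the raw 1.8 kg/m² with arm-specific SDs and r = 0.90 has 88%.

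**6. Drop-out step.** 126/(1 − 0.40) = 210, which is correct.

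**The case against.** The article discloses every mean and SD and both component effects, and it calls 0.42 a difference without labelling it a between-group Cohen's d. That is fair. But 0.42 is the only contrast given before the sample size, directly after a between-group d of 0.45, so a reader will take it as the design effect.

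On the sample size, the article relies on a cited method and does not say which contrast was tested, what sphericity value was used, or whether 0.42 or the raw means and SDs were entered. This objection stands. A reader might infer from the table that 126 is wrong, or that the trial was really sized for 0.32. Neither is shown. Unstated settings can reach 126 from 0.42, and the match at 0.32 holds only for the group-by-time test; change score, ANCOVA and slope give 87 to 108.

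A reader might also infer that the word conservative is false and that power collapses under non-adherence. The article uses the word about efficiency, complete-case analysis against a multilevel model, and in that sense gives a reason for it. The documents supply no non-adherence rate from which to work out a diluted effect. What remains is that the assumed effect itself comes from complete cases. The Phase 4 section ends measurement after more than 3 missed group sessions, so intervention completers are largely attenders. The claim of conservatism does not extend to the effect assumed.

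Finally, the effect-size definition under Statistical analyses could be read as making a comparison with usual care impossible. It does not: it refers to a single estimated baseline SD, and the comparison is tested through the treatment-time interactions. It does, however, define only change from baseline, so the subtraction of effects on separate SDs could recur if the SD is estimated by arm.

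**Conclusion.** The point holds in a limited form. The figure of 0.42 mixes two denominators and is not a between-group standardised effect. The difference in change is 1.8 kg/m², or d = 0.32 on the pooled baseline SD, with 0.26 to 0.375 as the range over the choice of arm SD. Set against the 2009 value of 0.45, the pooled figure is 28% lower (0.3245/0.45 = 0.72), where the text suggests near agreement.

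The 126 completers are not reproducible from 0.42 and the inputs as stated; they are not proven wrong. Nor is the trial shown to be underpowered: at 0.32, 126 completers give about 90% power for a group-by-time test, assuming sphericity, r = 0.90 and a linear separation of the arms. No change in patient numbers follows from this check.

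**What to change.** - **Sample size calculation, effect:** replace 0.42 with the difference in change of 1.8 kg/m² and d = 0.32, naming the SD (baseline, pooled 2:1, 5.55) and giving the range 0.26 to 0.375.
- **Sample size calculation, derivation:** state the contrast tested, the sphericity setting, the correlation and the effect actually entered to obtain 126. Keep 126 and 210. If 0.32 is confirmed as the input, say so; it should not be written in on inference alone.
- **Sample size calculation, conservative:** limit the word to the efficiency of complete-case analysis relative to the multilevel model, and note that the assumed effect was itself estimated in complete cases.
- **Statistical analyses:** add a between-group effect size, the difference in estimated change divided by one common baseline SD.

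The cost is text only, with no additional patients. The downside for the sponsor is that the quoted interim effect becomes less favourable.
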